#### Secondary outcomes

##### Psychosocial and lifestyle measurements

We applied a broad range of online questionnaires (see Table 4) to assess changes in subjective cognitive functioning (i.e., dysexecutive symptoms, attention and memory failures in everyday life), additional emotional wellbeing variables, mindfulness, fatigue, functioning, quality of life, and lifestyle behaviors. Furthermore, at the end of the interventions, all participants completed a questionnaire about whether they had experienced changes in cognition, emotional wellbeing, physical fitness, and quality of life, and, if so, they must rate the magnitude of either the improvement or deterioration. In the same questionnaire, we added some questions about the feasibility and acceptability of the interventions.

##### Anthropometric measures and physical fitness

Participants self-reported the values corresponding to height, weight, waist, and hip perimeters. Physical status and functioning (i.e., aerobic capacity, strength, flexibility, and balance) were evaluated with an adaptation of the Senior Fitness Test (Rikli and Jones, 1999). Detailed information on fitness tests is provided in Table 5.

**TABLE 5 T5:** Physical fitness components of the Senior Fitness Test (Rikli and Jones, 1999).

Component	Test
Aerobic endurance	2-min step test
Agility/dynamic balance	8-foot up-and-go test
Flexibility	
Lower body	Chair sit-and-reach test
Upper body	Back scratch test
Strength	
Lower body	30-s chair stand test
Upper body	30-s arm curl test

##### Brain magnetic resonance imaging

All images were obtained with a 3 Tesla scanner (Siemens Magnetom Verio Symo MR B17). Structural, functional, and diffusion sequences were acquired with the parameters described in Table 6. The participants who presented contraindications to performing MRI (e.g., pacemaker, valves, metals in the body, claustrophobia) were not evaluated.

**TABLE 6 T6:** Magnetic resonance imaging (MRI) and biological samples protocols.

MRI protocol	
**Sequence**	**Parameters**

T1-weighted multiplanar reformat sequence	Resolution: 0.9 × 0.9 × 0.9 mm, TR/TE: 1900/2.73 ms, slices: 192
T2-weighted turbo spin-echo sequence	Resolution: 0.7 × 0.5 × 3 mm, TR/TE: 6000/74 ms, slices: 35
T2-weighted turbo inversion recovery magnitude	Resolution: 1 × 0.8 × 3 mm, TR/TE: 9000/99 ms, slices: 44
Susceptible-weighted imaging with T2–fl3d sequence	Resolution: 1.1 × 0.8 × 2 mm, TR/TE: 28/20 ms, slices: 88
Resting state with a gradient echo planar imaging sequence	Resolution: 3.1 × 3.1 × 3 mm, TR/TE: 2000/25 ms, slices: 39, measurements = 240
Diffusion tensor imaging, echo planar imaging	Resolution: 2 × 2 × 2 mm, TR/TE: 10200/89 ms, directions: 64, inverse b0 pulse was added to obtain PA acquisition

**Blood sample protocol**	

**Process**	**Brief explanation**

Collection method	Blood samples were collected in vacutainer tubes containing EDTA disodium (anticoagulant) and were further processed to obtain plasma or frozen at −20°C
Plasma extraction and preparation	Platelet-poor plasma was separated by double centrifugation. Aliquots were frozen at −80°C for following analysis
Plasma analyses	Plasma parameters were measured by ELISA: IL-6, BDNF, IGF-1, Cortisol and VEGF values were obtained using kits from R&D Systems (Minneapolis, MN, USA), and CRP was analyzed by a turbidimetric method using reagents from RAL (Sant Joan Despí, Spain)
DNA extraction	DNA extraction was performed from 3 ml of frozen blood using the Chemagic DNA Blood Kit special [Chemagic MSMI (PerkinElmer, Waltham, MA, USA)]
DNA analyses	Polymorphisms in the APOE gene (single-nucleotide polymorphism rs429358 and rs7412) were determined using TaqMan methodologies

**Stool sample protocol**	

**Process**	**Brief explanation**

Collection method	Fresh stool samples were collected in plastic containers that were immediately put on ice
Preparation and storage	Aliquots were frozen at −80°C for subsequent analysis
DNA extraction	DNA extraction was performed from 200 mg of stool sample in the InviGenius Plus Instrument using the InviMag Universal Kit (Invitek, Berlin, Deutschland)
DNA analyses	The quantitative and qualitative analyses from the DNA was performed by spectrophotometry (Epoch, BioTek, Santa Clara, CA, USA)
SCFA determination	The determination of SCFA was carried out by gas chromatography combined with mass spectrometry

APOE, apolipoprotein E; BDNF, brain-derived neurotrophic factor; CRP, C-reactive protein; DNA, deoxyribonucleic acid; EDTA, ethylenediaminetetraacetic acid; ELISA, enzyme-linked immunosorbent assay; IGF-I, insulin-like growth factor I; IL-6, interleukin-6; MRI, magnetic resonance imaging; SCFA, short-chain fatty acids; VEGF, vascular endothelial growth factor.

##### Blood-sample and stool-sample data

We used a standard blood test to quantify hemograms, biochemical parameters, and lipid profiles. BDNF, IGF-I, vascular endothelial growth factor (VEGF), CRP, IL-6, and cortisol were analyzed in plasma, and genetic biomarkers on APOE were determined in the buffy coat fraction. Stool samples were collected to quantify species and subspecies of the intestinal microbiota, as well as the determination of short-chain fatty acids (SCFA). Specific details of the collection, storage, and analysis of the biological samples are included in Table 6.

### Exit qualitative interviews

We performed a qualitative study on a subset of participants (those with the highest adherence to interventions and willingness to participate) to know their experiences and evaluate the clinical significance of potential changes. We used standard guidelines (O’Brien et al., 2014) to develop the interview script and the data collection and analysis protocol.

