#### Statistical analysis

Statistical analysis will be carried out with IBM statistical package for the social sciences (SPSS) Statistics 27 and R environment. The same statistical pipeline will be run twice, in two sequential phases: (1) intention-to-treat analysis considering data from all randomized participants, including those that complete and drop out of the study (in case of missing values, an adequate method of imputation will be executed whenever appropriate, depending on the proportion of missing data and the missingness mechanisms); (2) per-protocol analysis including only those who have had a treatment adherence equal to or higher than 80%. The significant threshold will be set at a two-tailed *p*-value of 0.05, and an appropriate multiple comparisons correction method will be implemented.

Baseline demographic and clinical characteristics of participants in the different intervention groups will be described with central tendency, dispersion, and position measures and compared between the three groups using parametric or non-parametric tests. To address our primary hypotheses, we will use multiple regression models, which will include: (a) the difference between the follow-up and baseline values in the primary outcome measures as the explained variable; (b) the 3-arms intervention as the explaining variable, and (c) other confounding factors as covariates. We will consider sex, age, years of education, time since stroke, and the baseline score as fixed covariates. Moreover, we will contemplate the need to adjust for further unbalanced factors between groups that appear to correlate strongly with the outcomes. In case of violating the linear regression assumptions, transformations of the variables or methods of robust regression will be adopted. We will examine the secondary outcomes with the same pipeline in the per-protocol sample. Although the sample size was not calculated to allow interaction effects, we will examine potential mediator and moderator effects in this sample.

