## Discussion

The MindFit Project is a randomized controlled clinical trial that aims to assess the impact of mindfulness and PE combined with CCT on chronic stroke patients’ cognitive and emotional wellbeing. We predict that the three intervention groups will show improvements at the end of the trial, but we expect that these changes will be quantitatively and qualitatively different between groups. We expect that groups that have completed a combination of therapies will show more significant changes than those who have only done CCT. In addition, we hypothesize that there will be a different impact of mindfulness and PE on the cognitive and emotional domains.

Secondly, we plan to study the physiological mechanisms underlying the changes produced by mindfulness and PE through biomarkers to obtain evidence on the biological pathways affected by each intervention and the final effect on the structure and functioning of the brain. A final step in understanding the possible effects of our interventions will be to analyze which personal and clinical variables moderate their impact. In this regard, we will be able to determine which strategies are most suitable for each patient profile and thus lead stroke rehabilitation toward a personalized treatment model.

As a limitation of our study, we highlight the lack of a passive control group that prevents us from determining the efficacy of CCT alone. On the other hand, 3 months of intervention may not be enough to obtain robust and clinically meaningful results. There is a possibility that we will observe changes in biomarkers that are not reflected in behavior. Instead, there may be changes in cognition and emotional wellbeing that are not yet sufficiently established to see their molecular and brain correlates. Despite these limitations, the MindFit Project has the potential and ability to generate new knowledge at multiple levels of evidence, from molecular bases to behavioral changes associated with mindfulness and exercise therapies in chronic stroke patients. In addition, the integration of a qualitative perspective will help us understand the significance of these possible changes and their clinical relevance.

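### Patients' own evidence on clinical relevance is selected on adherence: the interviews take the most adherent volunteers, and the all-participant perceived-change ratings are assigned to the per-protocol sample

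*Protocol article*

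**What the plan says.** Four places in the protocol article bear on this.

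- **Exit qualitative interviews.** The subset interviewed, and the two purposes of the interviews, are given together: "those with the highest adherence to interventions and willingness to participate) to know their experiences and evaluate the clinical significance of potential changes". The subset size, its split by arm and the adherence cut-off are not given.
- **Discussion.** The closing paragraph says that "the integration of a qualitative perspective will help us understand the significance of these possible changes and their clinical relevance". The limitations named there are the lack of a passive control group and the short intervention. How interviewees were chosen is not among them.
- **Psychosocial and lifestyle measurements (secondary outcomes) and Table 4.** After the interventions "all participants completed a questionnaire about whether they had experienced changes in cognition, emotional wellbeing, physical fitness, and quality of life", and those who had noticed a change were told that "they must rate the magnitude of either the improvement or deterioration". Table 4 lists this as the Perceived Changes Questionnaire, 10 items, collected after the intervention only.
- **Statistical analysis.** The primary outcomes are analysed first by intention to treat and then in a "per-protocol analysis including only those who have had a treatment adherence equal to or higher than 80" per cent. The sentence on secondary outcomes names the per-protocol sample only.

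**The concern.** Adherence is observed after randomisation and may be tied to perceived benefit. People who felt no gain, felt worse or found the effort too great are plausibly the ones who did fewer sessions. Their accounts would show that a change did not matter, or was not worth its cost, and the interview rule leaves them out.

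As a description of how committed participants experienced the programmes, that sample is reasonable. The difficulty is the second task, evaluating the clinical significance of the trial's changes, because that is a statement about the randomised arms.

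The questionnaire given to everyone would be the natural counterweight, but the article sends it to the per-protocol sample with the other secondary outcomes. Read together, the two sections leave no planned report of patients' own ratings of change in the randomised arms as randomised. This matters most if the mean differences turn out small. The Discussion itself allows that three months may be too short for clinically meaningful results, and then turns to the qualitative work for help with relevance.

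**Working it through.** The plan states no figure on this point, so there is nothing to reproduce. The sample size of 47 per group plays no part in the argument.

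**Step 1: who supplies each piece of evidence.**

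| Evidence | Collected from | Analysed in | Selected on adherence? |
|---|---|---|---|
| Primary cognitive and emotional scores | All randomised | Intention to treat, then per protocol | No, in the first analysis |
| Perceived Changes Questionnaire | All participants | Per-protocol sample (adherence of at least 80%) | Yes, by the analysis rule |
| Quality-of-life scales | All participants | Per-protocol sample, as secondary outcomes | Yes, by the analysis rule |
| Exit interviews | Most adherent and willing | The same subset | Yes, by the sampling rule |

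The primary scores show how large a change is. The other three rows bear on whether patients found it worthwhile, and all three are conditioned on adherence.

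**Step 2: direction and possible size (illustration only).** Assume that adherence and perceived change are bivariate normal with correlation ρ, and keep the most adherent fraction f. Mean perceived change among those kept exceeds the mean of the whole arm by

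shift = ρ × φ(z) / f, in SD units,

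where z is the standard normal point with upper tail f and φ is the standard normal density.

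| f | ρ = 0 | ρ = 0.1 | ρ = 0.2 | ρ = 0.3 | ρ = 0.5 |
|---|---|---|---|---|---|
| 10% | 0 | 0.18 | 0.35 | 0.53 | 0.88 |
| 30% | 0 | 0.12 | 0.23 | 0.35 | 0.58 |
| 50% | 0 | 0.08 | 0.16 | 0.24 | 0.40 |

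The shift is upward for any positive ρ and zero when ρ = 0. A small interview subset is the top row. A per-protocol sample that keeps more than half of an arm would shift less than the bottom row.

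The same idea can be put as proportions. Suppose a share p of an arm perceives a worthwhile change, and those people are k times as likely to be selected. The share among those selected is kp / (kp + 1 − p). With p = 0.5:

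- k = 1: 0.5 / 1.0 = 50%
- k = 2: 1.0 / 1.5 = 67%
- k = 4: 2.0 / 2.5 = 80%

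The article supplies none of ρ, f, p or k. These figures show what follows from assumed inputs and do not estimate the bias in this trial.

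**Step 3: comparison between arms.** A shift common to all arms cancels in a difference. A comparison of arms is distorted only if selection differs between them. The Interventions section says that the combined programmes take about twice as long as the control programme, which is a reason why selection could differ. No adherence by arm is given, so this remains open.

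**Step 4: whether the planned model fits the questionnaire.** The regression takes follow-up minus baseline as the dependent variable and adjusts for the baseline score. A post-only questionnaire has no baseline, so that pipeline cannot be applied to it unchanged.

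**The case against.** Several counter-arguments are sound.

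- **The interviews are not decisive.** The Discussion says only that they will help in understanding relevance. No section makes them the sole basis, attaches a rule to them or compares arms with them. A reader might infer that a small mean difference will be declared clinically relevant on the testimony of the best adherers. The article does not say that.
- **Purposive sampling is accepted in qualitative work.** Willingness is unavoidable, and the article refers to a separate interview protocol that is not shown. The sampling rule is therefore not an error in itself. What stands is that the stated task reaches further than such a sample can support, and that the article does not say so.
- **Other relevance evidence is collected from everyone.** This is true of collection. As the article is worded, it is not true of analysis, because the secondary outcomes go to the per-protocol sample. The earlier sentence that the pipeline is run in both populations could be read as covering all outcomes, but the specific sentence on secondary outcomes names only one.
- **The link between adherence and benefit is not documented.** Correct. It is a plausible inference, and with no correlation the shift is zero.
- **The questionnaire has its own bias.** Also correct. Participants knew their arm, and the ratings are post-only self-reports. Relying on them without comment would bring in expectation bias where selection bias was removed.

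**Conclusion.** The point holds in limited form. Interviews with the most adherent volunteers are asked to evaluate clinical significance. The one instrument that asks every participant directly about perceived change is, as written, analysed only in those with at least 80% adherence. Patients' own evidence on relevance is therefore selected on a post-randomisation variable, and the article does not acknowledge it.

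The likely direction is towards benefit, on the assumption that adherence and perceived gain are positively related. The size cannot be computed from the document.

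Three stronger readings are tempting but unsupported:

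- **That the efficacy result is biased.** Randomisation, the primary outcomes and their intention-to-treat analysis are untouched.
- **That 67% to 80% is an expected result.** It restates assumed inputs.
- **That the top adherers in the combined arms are a more selected group than those in the control arm.** The doubled duration is stated, but adherence by arm is not.

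This is a matter of analysis population and interpretation, modest in weight and easy to correct.

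**What to change.** 1. **Questionnaire.** In the Statistical analysis section, state that the Perceived Changes Questionnaire will be reported by randomised arm in all randomised participants with follow-up data, as the proportions improved, unchanged and deteriorated, with the per-protocol version as supplementary. Give the number of respondents in each arm, since missing follow-up can itself select. Because there is no baseline value, specify a summary or model that does not need one.
2. **Statements on relevance.** Base them on these ratings together with the quality-of-life scales, reported in the same population. Say plainly that the questionnaire is an unmasked, post-only self-report open to expectation bias.
3. **Interviews.** Amend the Exit qualitative interviews section and the matching Discussion sentence so that interview findings describe the experience of highly adherent volunteers and are neither generalised to the randomised arms nor compared between them. Add the selection to the limitations.

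New interviews across adherence levels are not proposed, because data collection ended in December 2021.

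The cost is some wording and one analysis of data already in hand. The drawbacks are a possibly less favourable statement on relevance and reliance on a measure with the weakness named in item 2.

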### Analysis

#### Power analysis

Sample size calculations were conducted using the Granmo v7.12 software. Accepting an alpha risk of 0.05 and a beta risk of less than 0.20 in a bilateral contrast, 47 participants in each group are required to detect a minimum difference of 0.75 standard deviations between each pair of groups (assuming that there are three) after standardization of the variables to have mean 0 and standard deviation 1. This sample size supports a 20% tracking loss rate. We established a minimum effect size of 0.75 standard deviations by considering the results of meta-analyses studying the effects of mindfulness or PE on cognition or emotional wellbeing in stroke patients (e.g., Abbott et al., 2014; Oberlin et al., 2017; Ali et al., 2021; Sun et al., 2021). The effect sizes reported in these papers range from small-moderate (between *d* = 0.30 and *d* = 0.50) to moderate-large (between *d* = 0.50 and *d* = 1), depending on the intervention and the outcome studied. We used an intermediate effect size that was realistic to the literature and satisfied our trial’s practical and economic possibilities.

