## Aims of the study

The primary objective of the MindFit Project is to examine the effects of MBSR and PE on cognitive and emotional outcomes in chronic stroke patients by comparing three groups of participants who receive: MBSR + CCT, PE + CCT, or CCT alone. The primary hypotheses sustaining our main objective are:

(1)All three groups will experience gains at 3 months compared to baseline in cognitive functions and emotional status.(2)Given the study design (i.e., all three groups receive the same CCT treatment, with the only difference being the addition of either MBSR or PE), these improvements in cognition and emotion will be greater in the combined treatment groups than in the only CCT group (either to a greater extent in the same outcomes or different cognitive and emotional measures).(3)The add-on effects of MBSR and PE will differ from each other (i.e., they will have a specific profile of cognitive and emotional gains). Although there is a lack of studies comparing mindfulness and PE, we expect greater emotional gains after MBSR than PE, while PE will produce more cognitive benefits than MBSR.

The secondary objectives of the MindFit Project are:

(a)To study intervention-related changes in the molecular-cellular level (e.g., cardiometabolic, inflammatory, neurotrophic factors, gut microbiome species), the brain level [i.e., structural and functional magnetic resonance imaging (MRI)], and the behavioral level (e.g., physical activity and fitness status, mindful thinking, sleep quality, fatigue, quality of life).(b)To examine whether changes in the molecular-cellular, brain and behavioral levels mediate cognitive and emotional intervention-related changes.(c)To determine the genetic [i.e., apolipoprotein E (APOE) genotype], clinical (e.g., comorbidities, level of brain atrophy), sociodemographic (e.g., sex, age, educational level), and individual factors (e.g., cognitive reserve, general intelligence, personality), that moderate cognitive and emotional intervention-related changes.

A graphical representation of our objectives is presented in Figure 1.

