### Outcome variables

#### Primary outcomes

##### Cognitive functioning

All participants completed a comprehensive neuropsychological assessment. We will create z-score composites for each cognitive domain from normalized raw data, as well as a global cognitive function score based on the sum of all domains (see Table 3). Domains will be created following a theoretical-driven approach based on the literature (Lezak et al., 2012). We will consider the changes in cognitive domains and global cognition as primary outcome measures.

**TABLE 3 T3:** Neuropsychological assessment and proposed cognitive composites.

Composite		Test-subtest
Attention–Speed	Attention	Wechsler Adult Intelligence Scale III–Digits Forward (Wechsler, 2001)
		Trail Making Test–A (Tombaugh, 2004)
	Speed	Wechsler Adult Intelligence Scale III–Digit symbol coding (Wechsler, 2001)
Executive functions	Inhibition	Stroop Color and Word Test–Interference (Golden, 2001)
	Flexibility	Trail Making Test–B (Tombaugh, 2004)
	Fluency	PMR phonological verbal fluency (Peña-Casanova et al., 2009)
		Semantic verbal fluency of animals (Peña-Casanova et al., 2009)
	Working memory	Wechsler Adult Intelligence Scale III–Digits Backward (Wechsler, 2001)
Language		Boston Naming Test (15-items) (Goodglass et al., 2001)
Memory	Verbal memory	Rey Auditory Verbal Learning Test–Total learning (Schmidt, 1996)
		Rey Auditory Verbal Learning Test–Delayed recall (Schmidt, 1996)
	Visual memory	Rey-Osterrieth Complex Figure–Memory accuracy (Rey, 2009)
Visuospatial functions		Rey-Osterrieth Complex Figure–Copy accuracy (Rey, 2009)

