##### Emotional wellbeing

Depression, anxiety, and stress levels were measured through the Beck Depression Inventory (Sanz et al., 2003) and the Depression Anxiety Stress Scale (Bados et al., 2005). Detailed information on these questionnaires is provided in Table 4. We will consider the changes in these questionnaires’ total scores as primary outcome measures.

**TABLE 4 T4:** Questionnaires.

Name	No. of items	Domain or domains assessed
Beck Depression Inventory-II (Sanz et al., 2003)	21	Depressive symptoms
Childhood Adverse Experience International Questionnaire (World Health Organization, 2020) (baseline only)	36	Adverse childhood experiences
Clinical Outcome in Routine Evaluation-Outcome Measure (Feixas et al., 2012)	34	Psychological distress with four domains: subjective wellbeing, problems/symptoms, general functioning, and risk
Cognitive Reserve Questionnaire (Rami et al., 2011) (baseline only)	8	Cognitive reserve estimation based on proxies
Concomitant Therapies Questionnaire (post-intervention only)	15	Registry of other therapies that the participants follow concomitantly with the study interventions
Demographics and Health History (baseline only)	50	Demographics, medical story, consumption of alcohol and tobacco, COVID-19 data (infection and vaccination), female reproductive health (only in women), data important for microbiome analysis
Depression Anxiety Stress Scale (Bados et al., 2005)	21	Depressive, anxiety, and stress symptoms
Dysexecutive Questionnaire (Pedrero Pérez et al., 2009)	20	Dysexecutive symptoms
Expectancy Questionnaire (baseline only)	10	Expectations about treatment improvements in cognition, emotional wellbeing, physical fitness, and quality of life due to study interventions
Fatigue Assessment Scale (Cano-Climent et al., 2017)	10	Physical and psychological aspects of fatigue
Five Facet Mindfulness Questionnaire (Aguado et al., 2015)	39	Five factors of mindfulness: observing, describing, acting with awareness, non-judging of inner experience, and non-reactivity to inner experience
Food Frequency Questionnaire (Vioque and Quiles, 2003)	93	Frequency consumption of specific foods
Mediterranean Diet Adherence screener (Martínez-González et al., 2012)	14	Adherence to the Mediterranean diet
Memory Failures in Everyday Questionnaire (Montejo Carrasco et al., 2012)	28	Memory failures in daily life
Mindfulness Attention Awareness Scale (Soler et al., 2012)	15	Mindfulness (especially the “acting with awareness” component)

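### The 47 per arm gives 80% power at 0.75 SD for three arm contrasts on one outcome, but the protocol declares eight unranked primary outcomes

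*Protocol article*

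**What the plan says.** The power analysis of the protocol article opens with "Accepting an alpha risk of 0.05 and a beta risk of less than 0.20 in a bilateral contrast" and states that "47 participants in each group are required to detect a minimum difference of 0.75 standard deviations between each pair of groups". The difference is expressed "after standardization of the variables to have mean 0 and standard deviation 1", three groups are assumed, and the figure is said to allow for 20% loss. The effect size is justified as follows: "We used an intermediate effect size that was realistic to the literature".

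On cognition, the primary outcomes section says "We will consider the changes in cognitive domains and global cognition as primary outcome measures". Table 3 lists five composites (attention–speed, executive functions, language, memory, visuospatial functions), so with the global score there are six cognitive primary outcomes. On emotion, the change in two questionnaires' "total scores as primary outcome measures" adds a depression inventory and a depression–anxiety–stress scale. That is eight primary outcomes, and no order or hierarchy among them is given.

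Hypothesis 2 in the aims expects larger gains in the combined arms, "either to a greater extent in the same outcomes or different cognitive and emotional measures". The statistical analysis section sets a two-tailed 0.05 threshold and adds that "an appropriate multiple comparisons correction method will be implemented".

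**The concern.** The sample size uses its whole multiplicity allowance on the three arm contrasts of one variable. The outcome sections then declare eight such variables, so there are 8 × 3 = 24 primary contrasts. A correction is promised, but whichever scope it takes, one property of the design is lost. A correction across outcomes makes the stated power too high. A correction across arms only leaves the trial-wide error rate well above 5%.

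Data collection finished in December 2021, so the sample size is fixed. With eight equal-ranking primary outcomes and a hypothesis that can be read as met by a gain on any of them, the headline result could be chosen after the data are seen.

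**Working it through.** **Inputs.** From the power analysis: difference 0.75, SD 1, two-sided alpha 0.05, power 0.80, three pairs of groups, 20% loss. From the randomization section: 47 per arm, 1:1:1. From the outcome sections: 8 primary outcomes.

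**Step 1: reproduce the 47.** Normal approximation: n = 2(z(1−α/2) + 0.8416)² / 0.75², then divide by 0.8 for loss.

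| Contrasts adjusted for | α per contrast | z | n evaluable | n / 0.8 |
|---|---|---|---|---|
| 1 | 0.05 | 1.960 | 27.9 | 34.9 |
| 2 | 0.025 | 2.241 | 33.8 | 42.2 |
| 3 | 0.01667 | 2.394 | 37.2 | 46.5 → 47 |
| 24 | 0.00208 | 3.078 | 54.6 | 68.3 → 69 |

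Of the variants at or below three contrasts, only the adjustment for three gives 47. (Rounding 37.2 up to 38 before inflating gives 48, which makes no practical difference.) The calculation therefore covers three contrasts on one outcome.

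**Step 2: power if the correction spans the primary family.** Evaluable per arm after 20% loss: 47 × 0.8 = 37.6. Noncentral t with df = 3n − 3 and noncentrality 0.75 × √(n/2), which is 3.252 at n = 37.6 and 3.636 at n = 47. Bonferroni thresholds; no covariate gain.

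| Family | α per contrast | Power at 0.75 SD, 37.6 per arm | Power, 47 per arm | Difference for 80% power, 37.6 per arm |
|---|---|---|---|---|
| 3 (one outcome) | 0.05/3 | 79% | 89% | 0.76 SD |
| 6 (two outcomes) | 0.05/6 | 71% | 83% | 0.82 SD |
| 24 (eight outcomes) | 0.05/24 | 54% | 69% | 0.92 SD |

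**Step 3: error rate if the correction spans only the arms within each outcome.** Simulation under the global null: three arms, eight equicorrelated outcomes, each contrast tested at 0.05/3. The correlations are assumptions, since the protocol gives none.

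| Outcome correlation | Chance of at least one false positive |
|---|---|
| 0 | 30% |
| 0.3 | 27% |
| 0.5 | 23% |
| 0.7 | 18% |

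**Step 4: how far baseline adjustment could help.** The analysis model includes the baseline score. If 0.75 is in raw-score SD units (the protocol does not say) and the baseline–follow-up correlation is r, the effective difference is 0.75/√(1 − r²). At 0.05/24 and 37.6 per arm:

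- r = 0.5: 0.866, power 72%
- r = 0.6: 0.938, power 82%
- r = 0.7: 1.050, power 92%

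These correlations are also assumptions.

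**The case against.** The best defence is that 54% is the pessimistic end. It combines Bonferroni over 24, the full 20% loss and no covariate gain. Holm or resampling would lose less, particularly as the global score is the sum of the domains. A baseline correlation near 0.6 would restore 80% if 0.75 is a raw-score difference. If the aim is to detect at least one of several true effects, the chance is higher: for one active-versus-control comparison at 0.05/24, 37.6 per arm and outcome correlation 0.5 (assumed), about 79% with three affected outcomes and 91% with all eight. All of this stands and belongs beside the 54%. It does not rescue the power sentence, which claims 80% per pair and makes no allowance for more than one outcome.

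The correction method may properly be left to a statistical analysis plan, and its absence here is not the fault. The choice of primary outcomes and the power claim are both protocol content, and they do not fit together.

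Four stronger readings are tempting, but the document does not support them:

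- **That the 47 is an arithmetic error.** It reproduces.
- **That the tests will go uncorrected.** The analysis section promises a correction.
- **That success on any single outcome is the stated rule.** No success rule is written. This is an inference from the hypothesis 2 wording and the lack of a hierarchy.
- **That mindfulness and exercise cannot differ by 0.75 SD because the cited effects run from 0.30 to 1.00.** Those are example effects that vary by intervention and outcome, not bounds on each arm. An arm with no effect on an outcome where the other gains 1.0 would give a difference of 1.0, and hypothesis 3 expects such outcome-specific profiles.

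**Conclusion.** The concern holds as a mismatch of scope: the power statement describes one outcome and the protocol declares eight. For the 24 contrasts as declared, conservative per-contrast power at 0.75 SD is about 54% with the planned loss and 69% with none, and 80% power needs about 0.92 SD. If power is kept near 80% by correcting across arms only, family-wise error is about 18–30%, at least three times the nominal 5%. The power figures assume Bonferroni and no covariate gain; the error figures rest on assumed outcome correlations of 0.7 to 0. Covariate adjustment or a less conservative method could narrow the power gap, but the protocol claims no such gain in its calculation. The power sentence is wrong as written for the declared primary family and should be corrected.

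**What to change.** Before unblinding, issue a dated and disclosed amendment that says which outcomes form the confirmatory family, and restate power for that family. Two workable choices:

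- **Reduced family.** Global cognition and one emotional total score, with Holm over the six contrasts and the other six outcomes secondary. Power with 20% loss, before covariate gain and at the first Holm threshold: about 71% at 0.75 SD, or 80% at about 0.82 SD.
- **All eight kept.** One correction across all 24 contrasts. On the same Bonferroni basis: about 54% at 0.75 SD, or 80% at about 0.92 SD.

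If the sponsor wishes to claim a gain from baseline adjustment, the amendment should state the assumed correlation and whether 0.75 refers to raw-score or adjusted SD units. The hypotheses themselves need not be reworded.

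No patients are added. The price is a less favourable power figure and, under the first choice, a change of primary outcomes made after data collection, which must be disclosed as such. The article describes analysts as blind to allocation and the primary results as still to be reported. If unblinding has already happened, the amendment should say so.
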